**Methods/analysis:**

42 patients will be recruited who have been diagnosed with mild-to-moderate KOA and randomly allocated in equal proportions to traditional Chinese acupuncture or minimal acupuncture. They will receive acupuncture for 24 sessions over 8 weeks. The primary end point is success rate, which will be calculated according to a change from baseline in Western Ontario and McMaster Universities Osteoarthritis Index pain and function scores at 8 weeks. Secondary end points include pain and function measurement, global change, the quality of life and the use of non-steroidal anti-inflammatory drugs (Celebrex, Pfizer) at 8, 16 and 26 weeks.

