### Interventions

The acupuncture protocol follows the CONSORT^29^ and STRICTA.^30^ All acupuncturists have Chinese medicine practitioner licenses, and they have been qualified for at least 10 years. All acupuncturists will receive training in the application of MA. Celebrex will give to participants if their pain intensity ≥80 on a 10 cm visual analogue scale (VAS).^31^

The protocol specifies the intervention of acupuncture to be a 20 min treatment which is applied 3 times weekly for 8 weeks, with 24 sessions in total permitted. Disposable, sterile steel, 0.30×25 mm or 0.30×40 mm needles (Huatuo disposable acupuncture needle, Suzhou Medical Co., Jiangsu, China) will be used in two groups.

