## Outcomes

### Primary outcome measurement

Success rate will be calculated according to a change from baseline in Western Ontario and McMaster Universities Osteoarthritis Index (WOMAC)^32^
^33^ pain and function scores at 8 weeks. WOMAC function subscale (17 items, scored from 0 to 68) and pain subscale (5 items, scored from 0 to 20) with higher scores represent worse pain and function.

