### Secondary outcome measurement

Knee pain will be assessed by WOMAC pain subscale and Visual Analogue Scale (VAS, 0–100, higher scores representing worse pain). WOMAC function subscale will be used to measure physical function. Knee injury and Osteoarthritis Outcome Score (KOOS 0–100, higher scores indicating better function) subscales comprise pain, symptoms, activities of daily living and quality of life.^34^ Health-related quality of life will use the 12-item Short Form Health Survey (SF-12 0–100, higher scores representing better quality of life).^35^ The use of the NSAIDs (Celebrex, Pfizer) will be at 8, 16 and 26 weeks.

Adverse events will be monitored and reported by acupuncturists via open-ended questioning. Patients will be suggested to state any adverse circumstances they go through, comprising discomfort or bruise in the locations pierced by needle, nausea or the feeling of faint after the acupuncture treatment. Every crucial sign and adverse events are going to be investigated and recorded during every visit.

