### Statistical analysis

The results will be analysed by using the SPSS software (SPSS V.12.0 KO for Windows). The accepted level of significance will be p<0.05. Measurement data were expressed by mean number±SD, enumeration data expressed as a percentage.

The statistical analysis will be carried out based on the theory of intention-to-treat (ITT) analysis as well as per-protocol (PP) analysis. In the case of ITT analysis, missing data will be replaced according to the principle of the last observation carried forward and the maximum likelihood regression analysis. PP analysis will be conducted with patients who have received treatments >16 times and complete the case report form (CSF). χ^2^ Test is going to be performed for the situation of proportions; meanwhile, the analysis of independent sample t-tests is going to be conducted to examine the baseline discrepancies between the two groups. The significance of the differences in the various data in each group will be analysed with a paired t-test. On the basis of the baseline and temporary analgesic medicine dosage adjustment, continuous measurement results will be analysed using covariance test, and logistic regression analysis will be used for the two classification outcomes. Above two analyses will be present as difference in means or advantage ratio with 95% CIs.

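### Adjusting the main models for rescue analgesic dose, which follows randomisation and depends on pain, means they do not estimate the effect of assignment; the direction and size of the distortion cannot be known from the protocol

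*Protocol article*

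**What the plan says.** All places are in the protocol article.

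- **Statistical analysis, covariates:** "On the basis of the baseline and temporary analgesic medicine dosage adjustment, continuous measurement results will be analysed using covariance test". The same sentence continues: "logistic regression analysis will be used for the two classification outcomes". The adjustment clause opens the sentence, so its natural reading covers both models. The next sentence attaches 95% confidence intervals to these two analyses and to no others.
- **Statistical analysis, principle:** the analysis is to be intention-to-treat, with a per-protocol analysis alongside.
- **Statistical analysis, proportions:** a chi-square "Test is going to be performed for the situation of proportions". No covariates are named for it.
- **Interventions:** "Celebrex will give to participants if their pain intensity ≥80 on a 10 cm visual analogue scale (VAS". The cut-off and the scale length do not match and must be reconciled. For this point it matters only that supply is triggered by pain.
- **Secondary outcome measurement and abstract:** NSAID use is a secondary endpoint: "The use of the NSAIDs (Celebrex, Pfizer) will be at 8, 16 and 26 weeks".
- **Table 1:** NSAID use is marked at 8, 16 and 26 weeks, with no mark at baseline or day 0.
- **Primary outcome measurement:** the primary endpoint is binary: "Success rate will be calculated according to a change from baseline in Western Ontario and McMaster Universities Osteoarthritis Index (WOMAC", using the pain and function scores at 8 weeks.

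**The concern.** A covariate in a randomised comparison should be fixed before treatment can influence it. Rescue dose is not. A patient whose pain falls under the allocated needling is less likely to receive Celebrex, so the dose is partly a result of treatment. Holding it constant compares TCA and MA patients with equal rescue use, and randomisation did not make those groups alike. A TCA patient and an MA patient with the same rescue dose will tend to differ in their underlying tendency to pain.

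At stake are the adjusted difference in means and the odds ratio. These are the only effect estimates planned with confidence intervals, and they come from a pilot that the Discussion says will supply data for judging whether a large trial is practicable. A reader would take them as the effect of being assigned to TCA, which they are not.

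**Working it through.** **Is the covariate post-randomisation?** Interventions makes supply depend on pain during the trial. Table 1 has no NSAID entry before treatment. The abstract and the secondary outcomes list NSAID use as a result to be compared. The dose in the model is therefore measured after assignment and is itself an outcome.

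**No planned figure to reproduce.** The 42 patients (21 per arm) rest on clinical experience, with no effect size, SD or rescue rate. The size of the distortion can be explored only under assumptions.

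**Formula.** For a linear model,

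total effect = adjusted effect + γ × δ,

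where δ is the TCA minus MA difference in mean rescue dose and γ is the coefficient of dose in the adjusted model. If TCA lowers pain, δ is negative. When γ is positive (dose marks worse pain), the adjusted effect is nearer zero than the total effect. When γ is negative (dose mainly relieves pain), it is further from zero. When δ is 0, the two agree.

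**Simulation 1 (all inputs assumed).** Pain 0–100, SD 20, rescue-free TCA effect −10, 300,000 patients per scenario, baseline always in the model. The table uses mean pain 50 and a correlation of 0.6 between on-treatment and week-8 pain. Rescue is given above a threshold, or as a dose that rises with pain. Its benefit is in points per use or per dose unit.

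| Rescue rule | Benefit | δ | γ | Adjusted | Adjusted + γδ | Total (fitted) | Adjusted / total |
|---|---|---|---|---|---|---|---|
| Graded dose | 0 | −0.299 | 11.60 | −6.63 | −10.10 | −10.09 | 0.66 |
| Graded dose | 10 | −0.299 | 1.62 | −6.44 | −6.92 | −6.93 | 0.93 |
| Graded dose | 20 | −0.296 | −8.32 | −6.39 | −3.93 | −3.92 | 1.63 |
| Threshold 60 | 0 | −0.149 | 13.64 | −7.97 | −10.00 | −9.99 | 0.80 |
| Threshold 60 | 30 | −0.150 | −16.21 | −7.87 | −5.44 | −5.43 | 1.45 |
| Threshold 80 | 10 | −0.045 | 6.19 | −9.25 | −9.53 | −9.53 | 0.97 |
| Threshold 80 | 30 | −0.042 | −13.61 | −9.26 | −8.69 | −8.68 | 1.07 |

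- With graded dose the ratio is 0.77 at a benefit of 5 and 1.19 at 15. With threshold 80 and no benefit it is 0.93.
- Varying mean pain from 50 to 70 and the correlation from 0.3 to 0.8, the ratio ran from 0.30 to 2.87.
- The odds ratio for success behaves the same way under graded dose: 2.55 becomes 1.97 with no rescue benefit, and 1.59 becomes 2.00 at 20 points.
- With no true effect, both models gave 0.06, so there was no bias.
- Threshold 80 gave about 6.7% users on MA and 2.2% on TCA. With 21 per arm that is 0.067 × 21 = 1.4 and 0.022 × 21 = 0.5 patients.

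**Simulation 2 (all inputs assumed).** WOMAC pain 0–20, TCA effect −2, 400,000 patients per scenario, dose rising with latent pain, rescue worth c points at the mean dose among users. The adjusted coefficient does not depend on c, while the total effect shrinks linearly with c. The two meet at c* = (total at c=0 − adjusted) / (total at c=0 − total at c=1), in absolute values.

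| Users | Adjusted | Total, c=0 | Total, c=1 | Shrinkage, c=0 | Shrinkage, c=1 | c* |
|---|---|---|---|---|---|---|
| 10% | −1.72 | −2.00 | −1.88 | 14% | 9% | 0.28/0.12 = 2.3 |
| 20% | −1.53 | −2.01 | −1.79 | 24% | 14.5% | 0.48/0.22 = 2.2 |
| 30% | −1.36 | −2.01 | −1.74 | 32% | 22% | 0.65/0.27 = 2.4 |
| 50% | −1.04 | −1.99 | −1.65 | 48% | 37% | 0.95/0.34 = 2.8 |

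Above c*, the adjusted estimate lies further from zero than the total effect.

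**The case against.** **Direction.** A reader might infer that the adjusted effect is always too small. The protocol does not support that. Both simulations reverse once rescue is worth somewhat more than acupuncture itself: above about 2.2 to 2.8 points against an assumed effect of 2, and between 10 and 15 points per dose unit against an assumed effect of 10. The protocol gives no rescue benefit. This objection stands.

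**Size.** Supply is tied to high pain in a mild-to-moderate population, so few patients may qualify. With threshold 80 and mean pain 50 the ratio stays between 0.93 and 1.07. This stands as a possibility, but it depends on the assumed mean pain, and the protocol gives no rate. If use is that rare, the dose coefficient would rest on about two patients.

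**Reach.** A reader might also infer that the primary comparison is certainly affected. It may not be. The chi-square test has no covariates and could be the primary test of success rate, and extending the adjustment to logistic regression means interpreting an unclear sentence. Against this, the chi-square test shares its sentence with t-tests for baseline differences, so its role is uncertain, and no confidence interval is attached to it. The continuous outcomes are affected on any reading.

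**A different target.** The adjustment might be meant to show the effect without rescue. It does not recover that either: in the main scenarios of the first simulation the adjusted estimates were −6.4 to −9.4 against a rescue-free −10, because dose also carries unmeasured pain severity.

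**Consequence.** This is a small pilot with no power claim. The protocol does not say that the adjusted estimate will size the next trial, and with no true effect no bias appeared. False-positive claims are therefore not the worry; a mis-stated effect is.

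**Conclusion.** The covariate choice is wrong as written. The adjusted ANCOVA, and by the natural reading the adjusted logistic regression, condition on a consequence of treatment that is also a secondary endpoint. They do not estimate the effect of assignment and conflict with the intention-to-treat principle stated in the same section.

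If TCA has an effect, the distortion is toward zero when rescue dose mainly marks worse pain, and possibly away from zero when rescue is strongly effective. The range of 0.30 to 2.87 illustrates what assumed inputs can produce and is not a forecast. The distortion is small if rescue is rare. A fixed direction or percentage cannot be asserted without a rescue rate and a rescue benefit, and the protocol gives neither. The chi-square test, if it is the primary success-rate comparison, is not affected.

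Uncertainty about direction is no defence of the model: a reader of the results could not tell whether the estimate was too small or too large.

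**What to change.** In the Statistical analysis section, remove rescue analgesic dose from the covariates of the main ANCOVA and logistic models, and adjust for the baseline value only. State that outcomes are compared between arms regardless of rescue use. Analyse NSAID use between arms as its own endpoint at 8, 16 and 26 weeks, as already listed. Keep any rescue-adjusted model only as a labelled sensitivity analysis. In the first simulation, the baseline-only model recovered the total effect of assignment in every scenario.

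The cost is one rewritten sentence, with no new data and no new patients.

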### Ethics and dissemination

The protocol has been registered to ClinicalTrials.gov registry. Any revisions about the protocol will be documented in the ClinicalTrials.gov registry. Written informed consent will be obtained from all participants. The patients will be given adequate time to raise questions and to consider whether or not to involve in the study. We are going to publish the results of this trial in a peer-reviewed clinical journal to have widespread dissemination.

## Discussion

KOA is a common public health problem and a leading cause of disability. The results of this pilot study are going to concentrate on patients suffering from mild-to-moderate KOA and will investigate whether acupuncture can be a practicable and efficient therapy.

A suitable control group is critical for a well-designed clinical trial. On the basis of the literature review as well as clinical experiences, the acupoints in the MA group do not therapeutically affect KOA. Additionally, the dosage for acupuncture is sufficient. The protocol specifies the intervention of acupuncture to be a 20 min treatment which is applied 3 times weekly for 8 weeks, with 24 sessions in total permitted. Moreover, according to generality for the trial, the wide inclusion criteria will render it more possible that the participants fairly stand for those who have mild-to-moderate KOA. One potential limitation of this study is that acupuncturists are not blinded because of the nature of intervention. However, acupuncturists will not relate to the outcome assessments or data analyses.

The pilot trial will supply the clinical foundation as well as data that are demanded for evaluating the practicability for a large-scale RCT trial in the future.

### Trial status

This trial is currently recruiting participants.
